### Statistical Analysis

Data will be expressed as mean (standard deviation, SD) for normally distributed variables and frequency (%) or median (interquartile range, IQR) for categorical and or nonnormal variables. Continuous variables are checked for normality using the one sample Kolmogorov-Smirnov test. Distribution of variables between the 2 groups is compared using *t* test or Mann-Whitney nonparametric test in case of normality violation and reported as mean (SD). Categorical variables are compared using Pearson and chi-square tests. An intention-to-treat analysis of the results is used. Generalized linear models will be used to assess the relationships between outcomes and exposures (here vitamin D3 supplementation intervention) adjusted by appropriate covariates. Analyses will be performed using the software SPSS version 19 (SPSS Inc). *P* value of less than .05 is considered as significance level.

**Table 1 table1:** The steps of study analysis.

Proceedings		Stage
Obtaining written inform consent form and completing the questionnaire		Recruitment and completion of the questionnaire
Determining groups according to their status of vitamin DCollection of the laboratory samples Obtaining fasting blood samples. Assessment of serum concentration of vitamin D in Masjed-Solayman immediately and storing Shustar samples at −80°C		Classification
Obtaining fasting blood samples 3 months after termination of the intervention for those without maintenance vitamin D therapy (groups A1, A3, B1, and B3) and for all women at delivery time. Obtaining cord blood sample from all participantsStart of intervention Prescription of vitamin D according to various protocols (A1-3 and B1-3) for intervention groups		Replication of laboratory samples
Follow-up of pregnancy outcomes and neonatal calcium and vitamin D status		Follow-up
	
	

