## Methods

### Overall Study Design

This was a 2-phase population-based study. The first phase comprised a population-based cross-sectional study in which 1600 and 900 first trimester pregnant women attending health centers of Masjed-Soleyman and Shushtar, Khuzestan province, Iran were recruited using stratified multistage cluster sampling with probability proportional to size (PPS) method [33]. In the second phase of this study, within the framework of screening regimen, Masjed-Soleyman participants with vitamin D deficiency were assigned to a screening program versus Shushtar participants (as nonscreening arm) to assess the effectiveness of various treatment regimens. Pregnancy outcomes including preterm delivery, miscarriage, preeclampsia, gestational diabetes, and type of delivery and neonatal outcomes including birth weight (gr), head circumference (cm), height (cm), APGAR score 1, 5 minute, icterus, cord falling off time (day), serum calcium (mg/dl) level, and cord concentration of 25(OH)D (ng/ml) were recorded.

Shushtar participants (as nonscreening arm) served as controls and were followed till delivery and any adverse pregnancy outcomes were assessed.

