### The First Phase

In the first phase, pregnant women attending prenatal care centers of urban areas of Masjed-Soleyman and Shushtar were recruited from July 1-September 31, 2014. Due to the blinding purposes and to avoid contacts among study subjects [34], we chose 2 cities with similar cultural, geographic, nutritional habits, and sun exposure conditions; one of these cities was assigned to intervention.

Masjed-Soleyman County is in the northeast of Khuzestan province. Its area is 9/6327 km^2^ with a population of 103,369 people with Persian ethnicity. This is a sunny region with a hot and humid climate. Its altitude is 260 meters above sea level. In terms of geographical location, it is between 31°59′ E longitude and 49°17′ N latitude. Shushtar County is in the north of Khuzestan. Its area is 2436 km^2^ with a population of 192,361 people with Persian ethnicity. The climate is similar to Masjed-Soleyman. Its altitude is 150 meters above sea level. In terms of geographical location, it is between 48°20′ E longitude and 32°30′ N latitude.

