### The Second Phase

In the second phase of the study, to assess the effect of screening strategy on maternal and neonatal outcomes, Masjed-Soleyman participants were assigned to a screening program versus Shushtar participants acting as the nonscreening arm. Within the framework of the screening regimen, an 8-arm blind randomized clinical trial was undertaken to compare the effects of various treatment protocols. Due to the cost and complexity of the process, 800 pregnant women with vitamin D deficiency from Masjed-Soleyman were randomly allocated to 1 of the designed intervention programs according to the study Figure 1. The remaining women with vitamin D deficiency were referred to specialists for further treatments. Participants of Shushtar did not receive any vitamin D supplementation. However, the comparison of the basic confounders between the initial recruited sample in Masjed-Solayman and the women allocated to intervention indicated no statistically significant difference and hence no selection bias occurred during the allocation of treatment (Table 4).

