### Sample Size Calculation

A cluster sampling method with PPS procedure was assigned. Sample size was calculated in screening group (Masjed-Soleyman) using the following formula (Figure 2) and assumption, resulting in 1537 subjects.

The same steps (except for ε=0.2) were used for calculation of sample size in no screening group (Shushtar), resulting in 900 subjects. Using the cluster sampling method, 1600 and 900 first trimester mothers were selected from among those receiving prenatal care in health centers in urban regions of Masjed-Soleyman and Shushtar, respectively.

Since the prevalence of the specified event is untreated or unrecognized and the number of people who have the risk factor (P) is high in the population, consequently, sample size needed for screening is considered sufficient. In other words, we define a correction coefficient by (1/P) for estimated sample size (n), and then we expect n (1/P) number of people to find the 0.15 difference with 5% significance level.

To compare different regimens used for vitamin D deficiency in the screening group, the sample size in each group was calculated based on the following formula (Figure 3) and assumption:

Considering loss to follow up of 10%, a total number of 100 in each study group was considered adequate.

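### For prevalence and the between-city screening comparison, the named tests ignore the cluster sampling, one city per arm cannot separate screening from city, and the claimed city comparability contradicts Table 3

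*Protocol article*

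**What the plan says.** **Sampling.** Overall Study Design says that first-trimester women in both cities "were recruited using stratified multistage cluster sampling with probability proportional to size (PPS) method". Sample Size Calculation adds that they were "selected from among those receiving prenatal care in health centers in urban regions of Masjed-Soleyman and Shushtar, respectively". The number of centres and the number of women per centre are not given.

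**Assignment of screening.** The First Phase chooses two cities for similarity and to avoid contact between participants, and says that "one of these cities was assigned to intervention". The Second Phase sets out the comparison: "Masjed-Soleyman participants were assigned to a screening program versus Shushtar participants acting as the nonscreening arm". No random choice of city is described.

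**Analysis.** Statistical Analysis names the t test or Mann-Whitney test for continuous variables. It continues "Categorical variables are compared using Pearson and chi-square tests" and "Generalized linear models will be used to assess the relationships between outcomes and exposures", with covariate adjustment, at P<.05. The article mentions no cluster term, robust variance or survey weight.

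**City comparability.** The Results text says that Tables 2 and 3 show no significant difference between the two cities. Table 3 marks spouse education, accommodation, sun exposure, cream, gloves and veil as significant. The Limitations section lists four items. Neither clustering nor the single city per arm is among them.

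**The concern.** Two separate faults affect the same result.

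1. Women attending one health centre may resemble each other. Tests that count each woman as an independent observation then overstate the information in the sample. This affects the prevalence estimates, a stated objective, and the standard error of any difference between the cities.

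2. Screening and city are the same variable. Any difference in outcome between the cities, whatever its cause, appears in full as a screening effect, and the P value makes no allowance for it.

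The Research Questions section asks whether universal screening should be advised, and Clinical Endpoints makes the effect of screening a primary endpoint. A significant city difference, next to a statement that the cities are alike, could be read as evidence for that policy.

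**Working it through.** **Step 1. Was clustering allowed for in the sample size?** The text gives "resulting in 1537 subjects" for the screening city and 900 for the other with ε = 0.2, but the formula is in Figure 2, which is not shown. I tried the usual relative-precision form, n = deff × 1.96² × (1−P)/(ε² × P). I assumed ε = 0.15 for the screening city, because 0.15 is the difference named in the text.

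- P = 0.10, deff = 1: 1536.6 (that is, 1537) and, with ε = 0.2, 864.3, against the stated 900.
- P = 0.18, deff = 2: 1555.6 and 875.0, both within 3% of the stated figures.

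Both are plausible, so the visible text cannot show whether a design effect was used.

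**Step 2. Were independence tests actually used between the cities?** I recomputed Table 3 from its counts (900 versus 900) as a plain Pearson chi-square without continuity correction; printed values are in brackets.

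- Education .073 (.07); spouse education .010 (.01); accommodation .0044 (.004); gloves .0025 (.002).
- Spouse occupation .08 (.08); sunglasses .15 (.15); spouse smoking .28 (.28); occupation .46 (.46).

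The printed values reproduce, so the published city comparisons ignored clustering.

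**Step 3. Size of the clustering effect.** Neither the ICC nor the cluster size is in the document; both are assumptions. With deff = 1 + (m−1) × ICC, the real error of a nominal 5% test is 2 × [1 − Φ(1.96/√deff)].

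- m = 20, ICC = 0.01: deff = 1 + 19 × 0.01 = 1.19; √deff = 1.09; error 0.072.
- m = 80, ICC = 0.05: deff = 1 + 79 × 0.05 = 4.95; √deff = 2.22; error 0.378.

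A different assumed range (10 to 30 centres per city, ICC 0.005 to 0.05, 1600 versus 900 women, 10% outcome) gives a standard error ratio of 1.09 to 2.59 and an error of 0.07 to 0.45.

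**Step 4. One city per arm.** Two cities minus two arms leaves 2 − 2 = 0 degrees of freedom for between-city variance. For illustration, assume a 10% outcome, no screening effect and a between-city SD s. Then SE_true² = SE_naive² + 2s², and the error is 2 × [1 − Φ(1.96 × SE_naive/SE_true)].

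| Women | SE_naive | s = 0.01 | s = 0.02 |
|---|---|---|---|
| 1600 vs 900 | √(0.09 × (1/1600 + 1/900)) = 0.0125 | 0.19 | 0.43 |
| 900 vs 900 | √(0.09 × 2/900) = 0.0141 | 0.17 | 0.38 |

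Both rows are shown because 1600 were to be recruited in Masjed-Soleyman, while Tables 2 and 3 compare 900 with 900.

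**Step 5. Do the cities differ?** The chi-square values from Table 3 are 77.5 for sun exposure (3 df), 67.7 for veil (1 df) and 52.5 for cream (2 df). Dividing by the largest design effect in Step 3, 4.95, leaves 15.6, 13.7 and 10.6, still above the 5% critical values of 7.81, 3.84 and 5.99. Spouse education (13.27, 4 df), accommodation (8.10, 1 df) and gloves (9.15, 1 df) would not survive that division (2.68, 1.64 and 1.85 against 9.49, 3.84 and 3.84). They do survive division by 1.19 (11.15, 6.81 and 7.69).

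**The case against.** **The full analysis plan may handle clustering.** A journal article condenses, and a generalized linear model can be fitted with GEE or robust variance. That is fair for the model sentence. It does not rescue the t test, Mann-Whitney and chi-square tests, which the article names itself and, for Table 3, has already applied. No analysis plan can create degrees of freedom for city.

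**The harm is not proved.** A reader might infer that the standard errors are certainly too small. The document does not support that: no ICC or cluster size is given, and stratification may offset part of the loss. The claim is conditional on a net design effect above 1. Nor can one infer that the planning ignored clustering, since Figure 2 is not shown.

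**Not every analysis is affected.** A reader might extend the point to the eight-arm trial. There, women were randomised individually in permuted blocks within one city, so the objection does not carry over in the same way. The model sentence, whose exposure is vitamin D3 supplementation, fits that trial as well.

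**The two-city design is open and reasoned.** The article gives its reasons, reserves the word randomised for the eight-arm trial and plans covariate adjustment. Table 2 also shows the same median baseline vitamin D in both cities (11 ng/ml, P=.96). All of this stands. But similar baseline vitamin D does not make the cities alike in other causes of preterm delivery, gestational diabetes or hypertension, and adjustment removes only measured differences.

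**Conclusion.** The concern holds for the prevalence estimates and the between-city screening comparison.

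- **Certain from the document:** the sampling is clustered; the named tests assume independence and were used that way in Table 3; one city per arm means that no P value can separate screening from city; and the Results statement on city comparability contradicts Table 3.
- **Conditional:** the size of the error. The 7% to 38% range rests on assumed cluster sizes and ICCs. The 19% to 43% range (17% to 38% with 900 per city) rests on an assumed 10% outcome and an assumed between-city SD.

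The single city per arm is the stronger half, because it needs no ICC and no reanalysis can remove it. Adjusting for health centre repairs the standard error within the cities only.

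**What to change.** 1. Estimate prevalence separately by city with design-based methods: strata, health centre as primary sampling unit, PPS weights. Do not pool using the populations in The First Phase: those are county figures, while the sample is urban.
2. Analyse between-city outcomes with a generalized linear model using GEE or cluster-robust variance by recruitment health centre, adjusted for the six Table 3 imbalances.
3. Correct the Results statement so that it agrees with Table 3.
4. Report the screening result as a non-randomised two-city comparison whose P value excludes city-level variation, and add this to Limitations.

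**Cost.** No new participants are needed, and the study is at the analysis stage. If the net design effect exceeds 1, intervals become wider (about 1.1 to 2.2 times under the Step 3 assumptions), and the screening conclusion becomes more cautious. The article does not say that the health centre is recorded in the dataset, so it may have to be recovered from study records.

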### Definition of Study Outcomes

In this study the primary outcome was vitamin D deficiency measured as serum level of 25(OH)D and was categorized as: (1) severe deficient (<10ng/ml), (2) moderate deficient, (10-20ng/ml), and (3) normal status (>20ng/ml) [36].

Our secondary outcomes were as follows: Preterm delivery was considered as birth at less than 37 completed weeks of gestation [37]. Miscarriage was referred to as pregnancy loss prior to 20 weeks from LMP [38]. Preeclampsia was defined as systolic blood pressure >140 mmHg or diastolic blood pressure ≥90 mmHg and 24-hour proteinuria ≥0.3 g, started at >20 weeks [39]. Gestational diabetes mellitus referred to glucose intolerance first detected during pregnancy and was diagnosed according to the *International Association of the Diabetes and Pregnancy Study Groups (IADPSG)* criteria [40]. Premature rupture of membrane was considered as rupture of the fetal membranes before the onset of labor regardless of gestational age [41]. By type of delivery, we meant cesarean section or vaginal delivery. Birth weight (gr) was defined as weight at birth irrespective of gestational age [42].

APGAR score comprises 5 components including *appearance, pulse, grimace, activity, and respiration*, each of which is given a score of 0-2 and reported at 1 and 5 minutes after birth [43]. Neonatal icterus was defined as the yellowish discoloration of skin and sclera by bilirubin, usually first noted in the face and then the body [44]. Cord falling off time (day) is the separation time of remained umbilical cord after birth [45].

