### Clinical Endpoints

Primary endpoints are to find out the beneficiary impact of screening of pregnant women for vitamin D deficiency on pregnancy and neonatal outcomes and assessing the effect of supplementation with vitamin D on these outcomes. In the screening group, within the framework of randomized controlled trial, the endpoint was cord serum concentration of 25(OH)D to compare various doses, regimen, and routes for vitamin D supplementation in pregnancy.

In this regard, primary outcomes are gestational diabetes, preterm delivery, and pregnancy induced hypertension. Secondary outcomes are type of delivery and neonatal outcomes including birth weight (gr); head circumference (cm), height (cm); appearance, pulse, grimace, activity, respiration (APGAR) score 1, 5 minute, icterus, cord falling off time (day), serum calcium concentration (mg/dl), and cord levels of 25(OH)D (ng/ml).

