### Blood Assessments

Upon enrollment into the study, a fasting blood sample was obtained from all participants. Separated serum samples by centrifugation were transferred to the central laboratory of Masjed-Soleyman (cold chain was kept during storage and transfer processes). The serum samples of participants in Shushtar were stored and kept frozen at -80°C until assayed at the end of the study, but at that time the serum concentration of vitamin D of Masjed-Soleyman participants were promptly measured. Based on 25(OH)D levels, mothers were divided as severe deficient (<10ng/ml), moderate deficient (10-20ng/ml), and normal status (>20ng/ml) [1]. The scale to express 25(OH)D status results was according to ng/ml; each 1 ng/ml is equal to 2.496 nmol/L.

Those participants from Shushtar and those with serum vitamin D>20 ng/ml from Masjed-Soleyman served as controls and were followed until delivery. Subjects with severe and moderate vitamin D deficiency from Masjed-Soleyman were selected for the second phase of the study and were randomly allocated to one of the treatment modalities presented in Figure 1.

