Plasma 25(OH) vitamin D3 was assessed using enzyme-linked immunosorbent assay (ELISA) method and a kit of Immunodiagnostics Systems Ltd (IDS Ltd) by Auto Analyzer (Human Corporation, Germany). The sensitivity of the test was 5nmol/L and the intra and interassay coefficient of variations (CVs) were 3.37% and 3.891%, respectively. Calibration of the instruments was done as per the manufacturer's instructions and validation studies were done prior to the test. All measurements were done according to the standard operating procedures and samples were analyzed by a single technician using the same equipment throughout the study in a reference laboratory.

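### The outcome definition classes 25(OH)D at the entry cut-offs as primary, while Clinical Endpoints names cord concentration for the regimen comparison; the classes would cost power, so the sections should be reconciled in favour of the concentration

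*Protocol article*

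**What the plan says.** The protocol article describes the outcome of the randomised part in more than one way.

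- **Definition of Study Outcomes:** "the primary outcome was vitamin D deficiency measured as serum level of 25(OH)D and was categorized as: (1) severe deficient (<10ng/ml), (2) moderate deficient" (10-20 ng/ml), and normal (above 20 ng/ml). No sample (maternal or cord) and no time point is attached. Preterm delivery and gestational diabetes appear here as secondary.
- **Blood Assessments:** the same limits define entry. "mothers were divided as severe deficient (<10ng/ml), moderate deficient (10-20ng/ml), and normal status (>20ng/ml" ng/ml). Then "Subjects with severe and moderate vitamin D deficiency from Masjed-Soleyman were selected for the second phase of the study".
- **Clinical Endpoints:** within the randomised trial "the endpoint was cord serum concentration of 25(OH)D to compare various doses, regimen, and routes for vitamin D supplementation in pregnancy". The next paragraph says that "primary outcomes are gestational diabetes, preterm delivery, and pregnancy induced hypertension" and places the cord 25(OH)D level among the secondary outcomes.
- **Statistical Analysis:** gives t or Mann-Whitney tests for continuous variables, chi-square tests for categorical ones, and generalized linear models with covariates. It does not say which applies to 25(OH)D.
- **Sample Size Calculation:** 100 women per arm after allowing for 10% loss. The formula and its assumptions are in Figure 3, which is not shown.

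**The concern.** Comparing doses, routes and maintenance schedules is one of the study's research questions. All eight arms receive active treatment, so the contrasts are between regimens that may all raise 25(OH)D. If the class is the outcome, a woman at 21 ng/ml and a woman at 40 ng/ml count the same. The better the regimens work, the more women share the top class and the less the outcome can separate them.

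The section that formally defines the outcomes fixes the class. The section that names the regimen endpoint points to a concentration and then ranks it second. An analyst could follow either. A null result on the class could then be read as equivalence of regimens when it reflects the coarse outcome.

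**Working it through.** **The plan's own figure.** 90 / (1 - 0.10) = 100 per arm, so the stated 100 corresponds to 90 evaluable. The difference and SD behind the 90 cannot be reproduced, because Figure 3 is not shown. The significance level of 0.05 is taken as two-sided.

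**Power on the concentration (assumed SD 8 and difference 3.5 ng/ml).** Standard error = 8 × √(2/90) = 1.193. 3.5 / 1.193 = 2.935. Power = Φ(2.935 - 1.960) = 83.5%, before any gain from baseline adjustment. Simulation gives about 84%.

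**Power on above 20 or not, same data.** The proportion above 20 in each arm is Φ((mean - 20)/8). Power is from the two-proportion test, using the pooled standard error under the null.

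| Lower arm mean | Above 20, lower arm | Above 20, higher arm | Difference | Power |
|---|---|---|---|---|
| 22 | 59.9% | 75.4% | 15.5 points | 61% |
| 25 | 73.4% | 85.6% | 12.2 points | 53% |
| 30 | 89.4% | 95.4% | 6.0 points | 33% |

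**The same check without assuming an SD.** The difference with 80% power on the concentration is (1.960 + 0.842) × √(2/90) = 0.418 SD. Scored as above 20 or not, its power is 60% if half the women are above 20, 49% if 80% are, and 36% if 90% are.

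**Information kept, relative to a normally distributed concentration.** For one cut c with a proportion p below it, the share kept is φ(c)² / (p(1 - p)).
- Half above 20: 0.3989² / 0.25 = 64%.
- 80% above: 0.2800² / 0.16 = 49%.
- 90% above: 0.1755² / 0.09 = 34%.

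With all three classes the share is the sum over classes of (φ at lower limit - φ at upper limit)² / class proportion. Evaluated midway between the two arms in the table above, it is 64% for a lower mean of 22 and 51% for 25. For 30 it falls to 28%, because almost all women are then in the top class.

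**Noise at the cut-offs, with no true change.** The article reports that "the intra and interassay coefficient of variations (CVs) were 3.37% and 3.891%, respectively". Baseline is taken as log-normal from Table 2 (median 11, IQR 7-16), so log-SD = ln(16/7)/1.349 = 0.613. Two readings of the same true value were simulated.

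| Total CV | Moderate to above 20 | All deficient to above 20 | Severe to moderate |
|---|---|---|---|
| 3.891% (inter-assay) | 2.2% | 1.1% | 3.3% |
| 10% (assumed) | 5.7% | 2.7% | 8.3% |
| 20% (assumed) | 11.3% | 5.4% | 16.5% |

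The assay CV is a lower bound, since it omits variation within a woman over time. The expected crossing rate is the same in every arm randomised within a stratum.

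**The case against.** The strongest reply is that Clinical Endpoints already gives the regimen comparison a continuous cord-blood endpoint, and that generalized linear models are planned. On that reading the three classes only define status for the prevalence objective, and no information is discarded. Part of this stands: the continuous analysis is within the plan's reach. It does not settle the matter. The class is called primary without being limited to the prevalence phase, and cord concentration is listed as secondary directly after being named the endpoint. The analysis section accommodates both types of variable without choosing. A condensed article may leave outcome coding to the full protocol, but this is a conflict in what the article itself states.

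A second reply is that SD 8, a difference of 3.5 and means of 22-30 are assumed, and that a yes/no cut is harsher than three classes. Both points are fair. The result is a range, and the three classes keep more than the single cut.

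A reader might also infer a stronger point: that because outcome and entry share cut-offs, noise alone carries women from deficient to normal, and that most of the information is lost. The documents do not support it.
- At the documented CV about 1% of deficient women cross 20, and such crossings do not favour any arm within a stratum.
- More than half the information is lost only if roughly 80% or more of the women finish in one class, and no post-treatment rate is given.
- The outcome definition specifies neither a single repeat sample nor a rate of corrected deficiency. Table 1 has a delivery sample for all women as well as the three-month sample in the arms without maintenance.

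**Conclusion.** The concern holds as a conflict between two sections over the primary outcome, with a real cost in power if the class version is used. At 90 evaluable per arm, power falls from about 80-84% to roughly 33-61% when 25(OH)D is scored as above 20 or not. The size depends on the assumed SD, difference and share of women above 20, but the direction is the same throughout the range. Three classes soften the loss while the classes are well filled, and lose that advantage as women collect above 20. Noise crossing the entry cut-offs is not a ground for objection to the randomised comparison. This should be changed; it does not invalidate the trial.

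**What to change.** Reconcile Clinical Endpoints and Definition of Study Outcomes as follows:

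1. State that the outcome of the randomised comparison is the 25(OH)D concentration in ng/ml, on the log scale if skewed.
2. Name the sample (cord or maternal) and one time point common to the arms compared. The Intervention section and Table 1 word the maternal sampling differently, so they need to be aligned if a maternal value is chosen.
3. Compare arms within each severity stratum in the generalized linear model already planned, with baseline 25(OH)D as covariate.
4. Keep the three classes as a descriptive secondary outcome.
5. Say which of the remaining outcomes, including the three clinical events now called primary in one section, are primary for which comparison.

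A minimum-change rule is not needed for a randomised comparison. Crossing rates in Shushtar should not be used as a noise reference: it is a non-randomised city, and first-trimester and delivery samples there also carry true seasonal change.

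The cost is wording and a modest change of analysis, with no extra samples or participants. The article says that data are already being analysed, so the choice should be dated and declared, ideally before any arm comparison of 25(OH)D has been examined.
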